Second, a related resource issue is alternate exercise delivery models. As outlined above, three main exercise delivery models have been studied in men on ADT – supervised 1:1, group-supervised, and home-based programs; however, our group has conducted the only clinical trial directly comparing 2 exercise delivery models (supervised 1:1 and group supervised) in men on ADT [77]. This trial was a pilot study that demonstrated the feasibility of enrolling patients into a RCT of different exercise modalities along with high intervention adherence and study retention [77]. However, multiple comparative trials have been conducted in other settings [111, 112]. For example, a systematic review of 12 RCTs of almost 2000 patients in cardiac rehabilitation has shown similar benefits of home-based versus in-centre rehabilitation on exercise capacity, cardiac events, modifiable risk factors (lipids, blood pressure, etc.), and mortality [112]. Of note, adherence was greater among home-based compared to in-centre participants in those studies. Clearly, both models require significantly fewer resources for population-level delivery than the gold-standard of 1:1 supervised, facility-based training. In addition, these models of exercise delivery may have added benefits such as improved adherence or social interaction, yet these modalities have never been effectively and directly compared for clinical efficacy or cost-effectiveness in men on ADT.

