### Randomization

Patients will be allocated in a 1:1 ratio to treatment groups through a web-based central randomization scheme, with stratification on centre and prior duration of ADT (**<** 3 months vs. 3+ months). We are stratifying on duration of prior ADT as this has been shown to impact on subsequent declines in physical function and QOL as well as response to exercise [12, 115]. Randomization will occur following the baseline assessment. Once randomized, group-supervised participants will be scheduled to attend their first exercise session and home-based participants will be scheduled to attend an orientation session conducted by the RC and health coach. All participants will receive a study manual and basic exercise equipment (stability ball, mat, and resistance bands) to support program adherence.

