#### Group-supervised program

Participants in the group-supervised program will take part in classes led by a CEP/RKin 3 times per week for a period of 6 months. At each site, groups will commence as soon as 2 men have been randomized to a group and will grow to include 4–8 participants to ensure adequate supervision and progression. Participants will be provided with a set of resistance bands to support additional independent exercise.

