#### Health coaching

A growing body of research supports the effectiveness of the role a ‘health coach’ in chronic disease management [121, 123]. A health coach is a clinic-based health promoter trained to specifically stimulate and support initiation of and adherence to health behaviours (e.g., exercise, improved nutrition). Participants in the home-based arm of the intervention will work with a remote health coach, following a protocol adapted from Spring et al.’s successful trials in improving physical activity and weight loss [120, 121, 124, 125] as well as our prior experience in the phase II trial [101] and other trials by members of our group [126–129] (Additional file 3: Table S2). The health coach will meet with each home-based participant at study entry to help set goals and will make contact with participants every week to review uploaded exercise data in relation to goals. In addition to weekly contacts made via phone or electronic device, health coaches will meet face to face with participants once a month during the intervention period. This will support the development of alliance between participant and health coach and will include items that may not be possible in phone or electronic-based contact.

To enhance health coach-participant interactions, we will use specialized health promotion software for smartphones (an ‘app’) from NexJ Systems, Inc. (Toronto, Canada). Home-based study participants will receive smartphones, loaded with health monitoring and communication software and a wearable activity tracker (Fitbit) to use for the duration of the intervention. NexJ software effectively interfaces with Fitbit activity trackers to capture all of the features that the Fitbit tracks. Previous research demonstrates that Fitbit results are reliable, valid measurements of exercise adherence [130, 131]. These data will allow health coaches to better support participants, providing them with tools and suggestions for maintaining or increasing adherence based on Fitbit results.

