### Sample size calculation

A total of 200 participants (100 per arm) gives an estimated 81% power for analysis of the FACT-F and 6MWT for non-inferiority and will also provide accurate estimates of parameters related to secondary outcomes. Details are shown in Additional file 4: Methods. There are no planned interim analyses or early stopping rules.

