### Statistical analysis

#### Co-primary outcomes

The primary analysis will use a Bayesian analysis of covariance (ANCOVA) model to regress the change in FACT-F and 6MWT values between baseline and 6 months against the baseline value, the treatment group variable and variables representing stratification by centre and length-of-ADT. We will treat the high-intensity group (group supervised; higher level of supervision and greater resources) as the reference.

For each primary outcome, we will compute the Bayesian posterior probability that the low intensity group is non-inferior to the high intensity group (i.e., that the mean difference between groups is larger than the non-inferiority margin -**δ**). If either of these probabilities is large enough (i.e. > 97.5%) then we will declare the home-based group to be non-inferior for that outcome. One advantage of a Bayesian approach is that it allows us to assign posterior probabilities to the 4 possible outcomes of the study (illustrated in Fig. 3): (1) Home-based inferior only for 6MWT; (2) Home-based inferior only for FACT-F; (3) Home-based inferior for both outcomes; and (4) both non-inferior. Another advantage is that it allows a more useful presentation of individual results than a simple confidence interval or *p*-value: for example, we will be able to say that the mean difference lies below –**δ** (i.e., home-based is inferior) with probability X%, that it lies between –**δ** and 0 (i.e., home-based is worse but non-inferior) with probability Y% and that it is above 0 (i.e., home-based is better) with probability Z%. Finally, the outputs of the Bayesian model can be used as probabilistic inputs for the economic analysis. The Bayesian analyses will use non-informative priors, allowing the results to be data-driven and make direct probability statements about non-inferiority.

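### The primary model has no term for exercise class: if outcomes vary between classes in the group arm, non-inferiority is declared at the margin more often than the nominal 2.5%

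*Protocol article*

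**What the plan says.** Under Randomization, allocation is by individual: "Patients will be allocated in a 1:1 ratio to treatment groups", stratified by centre and by prior duration of ADT.

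Under Group-supervised program, men in that arm attend led classes three times a week for six months, and "groups will commence as soon as 2 men have been randomized to a group and will grow to include 4–8 participants". In the home arm there is no class. Under Health coaching, "Participants in the home-based arm of the intervention will work with a remote health coach".

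Under Statistical analysis, Co-primary outcomes, the change from baseline to 6 months in FACT-F and in 6MWT is regressed on "the baseline value, the treatment group variable and variables representing stratification by centre and length-of-ADT". On priors: "The Bayesian analyses will use non-informative priors". On the decision: "If either of these probabilities is large enough (i.e. > 97.5%) then we will declare the home-based group to be non-inferior", applied to each outcome.

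No other analysis in the article carries a class or leader effect. The correlations it names are within a person: an AR1 structure for the secondary outcomes and for the adherence models.

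Under Sample size calculation, "A total of 200 participants (100 per arm) gives an estimated 81% power for analysis of the FACT-F and 6MWT for non-inferiority". The details are referred to a supplement that is not at hand.

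**The concern.** The listed model treats all men as independent given their covariates. In the group arm, men in one class share a leader, a timetable, education sessions and each other's company for six months. Any difference between classes in how well the training works makes classmates' outcomes alike. That reduces the information carried by the group-arm mean.

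The structure is partially nested, because it exists in one arm only. The centre term removes average differences between centres for both arms together. It leaves differences between classes within a centre in the residual, where they are counted as independent noise.

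An understated posterior SD matters more in a non-inferiority trial with a fixed probability threshold. It makes it easier to clear 97.5% when the true difference lies at the margin, so the error favours the declaration that the trial hopes to make. The same model outputs are intended as probabilistic inputs to the economic analysis, so the understated uncertainty would carry over there.

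**Working it through.** **Inputs from the article:** 100 men per arm, a 97.5% posterior threshold, non-informative priors, and classes that grow to 4-8 in the group arm only. With flat priors the rule behaves like a one-sided 2.5% test, so the nominal false-declaration rate at the margin is 2.5% per outcome.

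**Assumed inputs:** class ICC of 0.01, 0.05 or 0.10 (none is stated), equal class sizes, equal total variance in the two arms, and no clustering in the home arm.

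**The plan's own figure.** The 81% power cannot be reproduced, because the article gives no margin, SD, assumed difference or dropout. Back-solving with a one-sided 2.5% level, a true difference of 0 and no dropout, 81% with 100 per arm implies margin/SD = (1.960 + 0.878) × √(2/100) = 0.401. This is used only for the power figures below.

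**Formulas**
- Design effect in the group arm: DE = 1 + (m − 1) × ICC.
- True SE / model SE: r = √((DE + 1)/2).
- False declaration at the margin: 1 − Φ(1.96/r).
- Coverage of a nominal 95% interval: 2Φ(1.96/r) − 1.

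Example, m = 6 and ICC = 0.05: DE = 1 + 5 × 0.05 = 1.25; r = √(2.25/2) = 1.061; 1.96/1.061 = 1.848; false declaration 3.2%.

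| Class size m | ICC | DE | r | False declaration | Coverage of 95% interval |
|---|---|---|---|---|---|
| 4 | 0.01 | 1.03 | 1.008 | 2.6% | 94.8% |
| 4 | 0.05 | 1.15 | 1.037 | 2.9% | 94.1% |
| 4 | 0.10 | 1.30 | 1.072 | 3.4% | 93.2% |
| 6 | 0.01 | 1.05 | 1.012 | 2.6% | 94.7% |
| 6 | 0.05 | 1.25 | 1.061 | 3.2% | 93.5% |
| 6 | 0.10 | 1.50 | 1.118 | 4.0% | 92.0% |
| 8 | 0.01 | 1.07 | 1.017 | 2.7% | 94.6% |
| 8 | 0.05 | 1.35 | 1.084 | 3.5% | 92.9% |
| 8 | 0.10 | 1.70 | 1.162 | 4.6% | 90.8% |

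**Simulation check.** The flat-prior rule was applied to 20,000 simulated two-arm comparisons per setting, without covariates. It gave 2.2-2.5% at ICC 0, 2.6-2.7% at 0.01, 2.8-3.4% at 0.05 and 3.3-4.7% at 0.10, in line with the formula.

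**Power, class size 6, true difference 0, margin/SD 0.401.** Two quantities must be kept apart.
- Model as listed, with clustering present but ignored: Φ(0.878/r) = 80.7% / 79.6% / 78.4% at ICC 0.01 / 0.05 / 0.10.
- Clustering modelled: Φ(2.838/r − 1.96) = 80.0% / 76.3% / 71.9%.

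The inflated error rates in the table belong with the first line. The second line is the price of restoring 2.5%, and it holds only if the 81% made no allowance for clustering.

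**The case against.** The strongest reply is that the ICC may be close to zero. Programs are individualized from baseline fitness. Delivery is standardized through staff training, a manual, monthly calls and audits. One to two sessions a week are done independently, supervised sessions taper in months five and six, just before the endpoint, and rolling entry means that classmates do not share one stable class for the whole period. All of this stands as a reason to expect a small ICC, and at 0.01 the effect is negligible. None of it shows that the ICC is zero, which is what the listed model assumes.

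A second reply is that an article may leave random effects to the analysis plan. Here, however, the article sets out the primary model term by term, and the point rests on those terms. An unseen document may add a class effect.

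Some stronger readings are tempting but not supported:
- **That the Background proves correlation.** It says that the delivery models "may have added benefits such as improved adherence or social interaction". This is tentative and covers both models. A benefit shared equally by all classes shifts the arm mean and creates no ICC. Only variation between classes does.
- **That the 81% power is overstated.** The calculation is in a supplement that is not shown, so whether it allows for clustering cannot be judged.
- **That men sharing a health coach add a known amount.** This is plausible, but the article gives no number of coaches and no caseload, so no figure or model term can be founded on it.

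**Conclusion.** The point holds in conditional form. The stated primary model assumes independence among men whom the design places in shared classes in one arm. For any positive class ICC, the error runs towards declaring non-inferiority too often.

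With classes of 4-8 the rate at the margin is 2.6-2.7%, 2.9-3.5% or 3.4-4.6% per outcome at an assumed ICC of 0.01, 0.05 or 0.10, against a nominal 2.5%. The range runs from negligible to material, and the documents do not say where in it the trial lies. A reader might infer that the intervals are certainly too narrow. That goes too far, because it depends on an ICC that nobody has stated.

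The change is worth making because it is cheap and alters little if the ICC is near zero. It does not put the design in doubt.

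**What to change.** - Record class and leader identifiers for every man in the group arm. Trainers already keep weekly plans and logs by participant or group, and weekly attendance is captured, so this adds little work.
- Add to the primary Bayesian ANCOVA a random effect for class (or leader) in the group arm only, with a separate residual variance in each arm.
- Fix the membership rule before analysis, for example the class first joined.
- State the prior on the cluster SD and check sensitivity to it. With 100 men in classes of 4-8 there would be about 100/8 ≈ 13 to 100/4 = 25 classes, so this prior may have some influence. Say how it fits with the stated preference for non-informative priors.
- Report the model without the class effect alongside.

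**Cost:** slightly wider intervals and, because of rolling entry, only approximate class membership. There is also a modest loss of power once clustering is modelled: with classes of 6, to about 80% / 76% / 72% at ICC 0.01 / 0.05 / 0.10, if the 81% made no allowance for clustering.

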**Fig. 3 Fig3:**
[figure not shown]
Illustration of Four Possible Scenarios in Non-Inferiority Testing for Proposed 2-Arm Trial. We will compare groups by means of ANCOVA using the baseline score as the covariate. After fitting a Bayesian model to each outcome, we will evaluate the probability in each of the 4 regions in the figure above. We can calculate the probability that: 1. Both the 6MWT and FACT-F fatigue scores are non-inferior in the home-based arm. This is the green region (**b**). 2. Both the 6MWT and FACT-F fatigue scores are inferior in the home-based arm. This is the grey region (**c**). 3. The 6MWT score is non-inferior in the home-based arm. This is the green region (**b**) plus the blue region (**a**). 4. The FACT-F Fatigue score is non-inferior in the home-based arm. This is the green region (**b**) plus the gold region (**d**). If either probability in (3) or (4) is above 97.5%, then we will declare non-inferiority of the home-based intervention.

Since this is a non-inferiority trial, the primary analysis will be per protocol, which in the presence of non-adherence to exercise is more conservative than intention-to-treat (i.e., less likely to conclude groups are similar when they are not). Two secondary analyses of the primary outcomes will be conducted. First, we will make the above between-group comparison of the changes in FACT-F and 6MWT scores from baseline to each follow-up time point. Secondly, we will perform an intention-to-treat analysis, including outcomes on subjects who were non-adherent to their exercise program. We will also conduct within-group analyses of change over time for the co-primary outcomes to understand the effects of each exercise modality on these outcomes and to facilitate comparisons with published studies.

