#### Analysis

Cumulative costs and QALYs for each trial arm will be estimated and compared in order to calculate the incremental cost utility ratio, and incremental Net Health Benefit. Censoring for both outcomes will be handled through inverse probability weighting [178, 179].

We will evaluate uncertainty and estimate confidence intervals around the estimates, using both deterministic and probabilistic methods. We will account for correlation between costs and health outcomes using appropriate bivariate methods. Cost-effectiveness acceptability curves (CEACs) will be used to graphically represent the probability that the intervention would be cost-effective for thresholds of $20,000, $50,000, and $100,000 per QALY gained (multiple thresholds for sensitivity analyses). Reporting will follow the Consolidated Health Economic Evaluation Reporting Standards (CHEERS) statement [180].

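### The four joint FACT-F/6MWT probabilities are to be read off models fitted per outcome, which do not determine them; the protocol should name a bivariate model

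*Protocol article*

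**What the plan says.** Under Statistical analysis, Co-primary outcomes, the article describes the model thus: "The primary analysis will use a Bayesian analysis of covariance (ANCOVA) model to regress the change in FACT-F and 6MWT values", with the baseline value, arm, centre and ADT duration as covariates. It adds that "The Bayesian analyses will use non-informative priors".

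It gives as one advantage of this approach that "it allows us to assign posterior probabilities to the 4 possible outcomes of the study", and lists the four: inferior on 6MWT only, on FACT-F only, on both, or on neither.

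The Fig. 3 legend states the route to those probabilities: "After fitting a Bayesian model to each outcome, we will evaluate the probability in each of the 4 regions in the figure above". There, region b is both non-inferior, c is both inferior, a is non-inferior on 6MWT only, and d is non-inferior on FACT-F only.

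The declaration rule is per outcome. The Methods text says: "If either of these probabilities is large enough (i.e. > 97.5%) then we will declare the home-based group to be non-inferior for that outcome". The legend applies the same threshold to a+b (6MWT) and b+d (FACT-F).

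The article also says that "the outputs of the Bayesian model can be used as probabilistic inputs for the economic analysis". In the cost-effectiveness section it plans, for a different pair of quantities: "We will account for correlation between costs and health outcomes using appropriate bivariate methods".

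**The concern.** Table 1 schedules FACT-F and 6MWT for every man at baseline and at 6 months, so the two change scores are paired within person. The four regions are joint statements about two arm effects estimated from the same men. A model fitted to each outcome gives the posterior of each arm effect separately. It therefore gives P(a+b) and P(b+d), but says nothing about how the two effects vary together, and P(b) and P(c) depend on that.

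The simplest way to carry out the legend's wording is to pair draws from two separately fitted models, or to multiply the two probabilities. Either step assumes independence without saying so. The four-region summary is the only quantity described for the primary analysis that addresses both co-primary outcomes together, so it should rest on a model that can supply it.

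**Working it through.** **Inputs.** From the article: 100 men per arm, 1:1 allocation, non-informative priors, an ANCOVA adjusted for baseline, arm, centre and ADT duration, and a 97.5% threshold. Not in the article: any correlation between the FACT-F and 6MWT changes, or numerical margins and SDs. The correlation ρ is therefore assumed, over 0.2 to 0.7 with 0.5 as a middle value. The article gives no region probability to reproduce. Its 81% power figure is not needed for the region calculation.

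**Step 1: what the single-outcome probabilities leave open.** Let p and q be the posterior probabilities of non-inferiority on 6MWT and FACT-F. Without a dependence assumption, P(b) can lie anywhere from max(0, p+q−1) to min(p, q):
- p = q = 0.50: 0 to 0.50
- p = q = 0.80: 0.60 to 0.80
- p = q = 0.975: 0.95 to 0.975

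**Step 2: the correlation that matters.** With n men per arm, each adjusted arm effect is close to a difference of two mean residuals, with variance 2σ²/n. The covariance of the two effects is about 2ρσ₁σ₂/n. Their correlation is therefore about (2ρσ₁σ₂/n) / (2σ₁σ₂/n) = ρ, the within-man residual correlation. Simulated trials of 100 per arm, with a separate ANCOVA per outcome, agree: the estimated effects correlated at 0.21, 0.41 and 0.50 for residual correlations of 0.2, 0.4 and 0.5.

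**Step 3: the regions.** Take the joint posterior as bivariate normal with correlation ρ:
- P(b) = Φ₂(z_p, z_q; ρ)
- P(c) = 1 − p − q + P(b)
- P(a) = p − P(b) and P(d) = q − P(b)

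Under independence, P(b) = pq. Whatever P(b) gains over pq, P(c) gains too, and a and d each lose.

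With p = q (percent; the joint columns are for ρ = 0.2 / 0.5 / 0.7):

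| p = q | Both non-inferior: product | joint | Both inferior: product | joint | Error (points) |
|---|---|---|---|---|---|
| 0.50 | 25.0 | 28.2 / 33.3 / 37.3 | 25.0 | 28.2 / 33.3 / 37.3 | 3.2 / 8.3 / 12.3 |
| 0.80 | 64.0 | 65.7 / 68.7 / 71.3 | 4.0 | 5.7 / 8.7 / 11.3 | 1.7 / 4.7 / 7.3 |
| 0.90 | 81.0 | 81.7 / 83.2 / 84.7 | 1.0 | 1.7 / 3.2 / 4.7 | 0.7 / 2.2 / 3.7 |
| 0.975 | 95.06 | 95.16 / 95.46 / 95.83 | 0.06 | 0.16 / 0.46 / 0.83 | 0.1 / 0.4 / 0.8 |

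The first row can be checked by hand. At p = q = 0.50, P(b) = 1/4 + arcsin(ρ)/(2π). For ρ = 0.5 this is 0.25 + 0.5236/6.2832 = 0.333.

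**Step 4: when it shows.** The simulation assumed ρ = 0.5 and a standard error that gives 81% power per outcome (margin / SE = 1.96 + 0.88 = 2.84). The independence error reached 5 points or more in about 41% of trials when both true differences lay at the margin, about 13% when both lay at half the margin, and under 1% when both were zero. At ρ = 0.2 it cannot reach 5 points, because its maximum, at p = q = 0.50, is 3.2.

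**Step 5: the decision rule.** The 97.5% threshold is applied to p and to q. Neither depends on ρ, so the effect on the declarations is nil.

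**The case against.** The strongest reply is that the documents never say the outcomes are treated as independent or that probabilities are multiplied. The case rests on one clause of a figure legend. The Methods text speaks of a Bayesian model in the singular, which could be a joint model with its own baseline for each outcome. Residual covariance is often left to a full analysis plan, which is not shown.

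This stands against the stronger reading a reader might reach, that the protocol assumes independence and its reported probabilities will be wrong. The documents support neither half of that. Nor must the regions be products, since a dependence structure could be supplied when the posteriors are combined. The reply does not remove the point, however. The legend goes beyond silence: it states a method, one model per outcome, and that method does not yield the quantity promised. If a joint model is intended, the legend misdescribes it and needs the same correction.

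A second reply is that nothing hangs on it. No threshold attaches to both-non-inferior or both-inferior, the correlation is assumed, and the largest errors occur where non-inferiority is plainly not established. This also stands, and it sets the severity.

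A third concerns the economic analysis. The article says only that the Bayesian outputs can be used there. The evaluation it describes rests on EQ-5D-5L utilities and costs, and does not name FACT-F or 6MWT as inputs. A carried-over error is therefore conditional on both arm effects being used together as independent draws.

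**Conclusion.** The point holds as a minor one. The route given in the Fig. 3 legend does not determine the four joint probabilities promised in the Methods text. If the separate posteriors are combined as independent and the outcomes are positively correlated, both-non-inferior and both-inferior are understated and each mixed region is overstated by the same number of points. For an assumed correlation of 0.2 to 0.7, that is 3.2 to 12.3 points at single-outcome probabilities of 0.50, 1.7 to 7.3 at 0.80, 0.7 to 3.7 at 0.90, and under 1 at 0.975. A negative correlation would reverse the signs.

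The sizes rest on the assumed correlation, an approximately bivariate normal posterior and equal single-outcome probabilities. A reader might infer that the primary non-inferiority conclusion is compromised. It is not: only the four-region summary, and any joint use of the two arm effects in the economic analysis, is at stake.

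**What to change.** In the Fig. 3 legend, replace the wording about a model for each outcome with one bivariate Bayesian ANCOVA, and say the same in the Methods text. Regress the FACT-F and 6MWT changes together, each on its own baseline, arm, centre and ADT duration, with an unstructured 2×2 residual covariance and the non-informative priors already planned. Compute the four region probabilities from the joint posterior draws of the two arm effects. If both effects feed the economic analysis, pass the joint draws. Keep the 97.5% rule on the single-outcome posteriors.

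The cost is a sentence of text, one extra correlation parameter and slightly more modelling work. It needs no further data, participants or visits, and the single-outcome results should change little.

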Given the gaps in the published evidence, we recently conducted a phase II trial to assess the feasibility and efficacy of these 3 delivery models in a 6-month intervention [113] (manuscript submitted). The preliminary results suggested that group-supervised exercise and home-based exercise were generally non-inferior to 1:1 supervised exercise for both QOL and fitness outcomes. Specifically, group-supervised exercise was shown to have less than a 20% probability of being inferior to 1:1 exercise for 2 of 3 QOL and 3 of 3 fitness outcomes. The home-based arm had less than a 25% probability of being inferior to the 1:1 arm for 1 of 3 QOL and 3 of 3 fitness outcomes. Moreover, the home-based arm was associated with the highest adherence based on accelerometry. Altogether, this provided a foundation to refine our phase II protocol and conduct the present phase III trial, in which we decided to directly compare 2 exercise delivery methods that are least resource intensive. Although efficacious, the 1:1 supervised intervention arm appeared to provide minimal benefit over a group-supervised program and is cost-prohibitive within a publicly funded health care system.

The primary aims of this phase III non-inferiority RCT are:i.To determine, in men with PC on ADT, whether a home-based supported exercise program is non-inferior to a group supervised in-centre (facility-based) exercise program on the primary outcomes of fatigue and functional endurance;ii.To examine adherence to exercise and predictors of adherence in each exercise group during the 6-month intervention and for 6 months after program completion;iii.To conduct an economic analysis comparing both exercise interventions and usual care.

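### The Fig. 3 legend and the main text give different decision rules: the legend lets one passing co-primary outcome support a claim for the whole home-based intervention

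*Protocol article*

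**What the plan says.** Four places in the protocol article bear on the rule.

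- **Statistical analysis, Co-primary outcomes (main text).** The rule is outcome by outcome: "If either of these probabilities is large enough (i.e. > 97.5%) then we will declare the home-based group to be non-inferior for that outcome". The same section lists four possible study results and keeps the mixed ones apart from full success: "1) Home-based inferior only for 6MWT; (2) Home-based inferior only for FACT-F; (3) Home-based inferior for both outcomes; and (4) both non-inferior".
- **Fig. 3 legend.** The legend has its own numbered list. Item 3 is the probability for the walk test: "The 6MWT score is non-inferior in the home-based arm. This is the green region" (b) plus the blue region (a). Item 4 is the probability for fatigue: green (b) plus gold (d). It closes with the rule "If either probability in (3) or (4) is above 97.5%, then we will declare non-inferiority of the home-based intervention".
- **Background, primary aims.** The first aim asks whether the home programme "is non-inferior to a group supervised in-centre (facility-based) exercise program on the primary outcomes of fatigue and functional endurance".
- **Sample size calculation.** 100 participants per arm "gives an estimated 81% power for analysis of the FACT-F and 6MWT for non-inferiority", with details referred to Additional file 4, which is not shown.

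**The concern.** The two rules have the same trigger (either probability above 97.5%) but attach different claims to it. The main text licenses a statement about one named outcome. The legend licenses a statement about the intervention. They agree when both outcomes pass or neither does, and they part when only one passes. In that case the main text supports non-inferiority on, say, fatigue alone, while the legend supports calling the home-based programme non-inferior even if functional endurance is worse by more than its margin.

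Both rules are printed as current text and neither is given precedence. After the data are seen, a mixed result could be reported either way with support from the protocol. The trial is meant to inform publicly funded exercise programmes, so the headline conclusion should not depend on which page is cited.

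**Working it through.** **1. What the legend's probabilities contain.** From the legend: b = both non-inferior, c = both inferior, item 3 (6MWT non-inferior) = b + a, item 4 (FACT-F non-inferior) = b + d. By subtraction, a = 6MWT non-inferior with FACT-F inferior, and d = FACT-F non-inferior with 6MWT inferior. Regions a and d are the two mixed results that the main text lists separately from success on both. An intervention-level claim triggered by item 3 or item 4 alone does not exclude them. This step needs no numbers.

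**2. Inputs for the size.** From the article: 100 per arm, 81% power, threshold 97.5%, non-informative priors. Assumed: 81% is power per outcome at a true difference of zero; a posterior probability above 97.5% behaves like a one-sided 2.5% test; the two test statistics are bivariate normal with correlation r from 0 to 0.7.

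**3. The plan's own figure.** The 81% cannot be reproduced, because the margins, standard deviations and drop-out allowance are not in the article. Solving backwards, margin/SD = (1.960 + 0.878) × √(2/100) = 2.838 × 0.1414 = 0.401. That is plausible for a per-outcome figure but does not verify it.

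**4. Set-up.** Each statistic Z has mean 0 when the true difference is exactly at the margin, and mean 2.838 when the arms are equal. An outcome passes if Z > 1.960. Then P(either) = P(first) + P(second) − P(both).

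**5. One outcome at its margin, arms equal on the other.** At r = 0, P(both) = 0.81 × 0.025 = 0.0202, so P(either) = 0.81 + 0.025 − 0.0202 = 0.8148. At r = 0.7, P(both) = 0.0250 and P(either) = 0.8100. The legend's rule therefore yields an intervention-level claim with probability 81.0% to 81.5%; requiring both gives 2.0% to 2.5%. If the worse outcome lies 1.5 margins below zero, its own chance of passing is 1 − Φ(1.960 + 1.419) = 0.0004, and P(either) is still 81%.

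**6. Both outcomes at their margins.** At r = 0, P(either) = 0.05 − 0.025² = 0.0494. At r = 0.7, P(both) = 0.0083 and P(either) = 0.0417. The range is 4.2% to 4.9%, against 2.5% for each outcome-specific claim.

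**7. Arms equal on both outcomes.**

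| r | Either passes | Both pass |
|---|---|---|
| 0 | 96.4% | 0.81² = 65.6% |
| 0.5 | 91.9% | 70.1% |
| 0.7 | 89.4% | 72.6% |

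**The case against.** The strongest reply is that the main text holds the operative rule and that it is sound. It confines the declaration to the outcome that passed and names the mixed results as distinct findings. It also promises, for each outcome, the probabilities of being inferior, worse but non-inferior, and better. The legend too reports the regions separately, so its last sentence may simply lack a limiting phrase. A clearly worse walk test would be visible in the planned results. All of this stands, and it settles what kind of defect this is: inconsistent wording, not a wrong choice of analysis. It does not remove the defect, because the legend's sentence is explicit, complete in itself and about the intervention.

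A reader might infer more than the documents support, in four ways:

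- **That the trial has adopted an either-outcome success rule.** It has not; that is the legend alone, and the main text says otherwise.
- **That the first aim obliges both outcomes to succeed.** It names both but does not say so. Requiring both is one defensible repair, not something the protocol already commits to.
- **That the 81% is wrong or undefined.** The article refers the details to Additional file 4, which may say which claim it covers. No error can be alleged.
- **That the region probabilities ignore the correlation between outcomes.** The legend says "After fitting a Bayesian model to each outcome, we will evaluate the probability in each of the 4 regions", which does not exclude a joint fit. The two probabilities that trigger a declaration are marginal, so correlation does not alter them.

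It is also fair that two separately named outcome claims, each at 97.5%, need not be adjusted for multiplicity. The 4.2% to 4.9% applies only to the legend's intervention-level claim.

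**Conclusion.** The concern holds as a contradiction between the main text and the Fig. 3 legend over what may be declared when only one co-primary outcome passes. The main text says "then we will declare the home-based group to be non-inferior for that outcome"; the legend extends the same trigger to the intervention. Followed as written, the legend permits an intervention-level claim while the home-based arm is inferior on the other outcome.

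The logical point rests on the text alone. Its size, about 81% with one outcome at its margin and 4.2% to 4.9% with both at theirs, depends on reading 81% as per-outcome power (first figure only), on equating the 97.5% posterior threshold with a one-sided 2.5% test, and on assumed correlations of 0 to 0.7. Under the main-text rule the problem does not arise. The rule governs the headline conclusion of a phase III trial, so it should be settled before analysis.

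**What to change.** Bring the legend into line with the main text by ending its last sentence with a restriction to the outcome whose probability passed. This is a change of a few words and costs no power and no data.

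If an intervention-level claim is also wanted, add one sentence: the home-based intervention is declared non-inferior only if both marginal posterior probabilities exceed 97.5%. No multiplicity adjustment is then needed, and a single pass supports a claim for that named outcome only. The cost is power. If 81% is per outcome, power for the joint claim is about 66% (r = 0) to 73% (r = 0.7), and that figure should be given beside the 81%. For scale, 81% power for both with independent outcomes needs √0.81 = 90% per outcome, or about 100 × ((1.960 + 1.282)/2.838)² ≈ 131 evaluable per arm. The first repair alone resolves the contradiction.
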